### Secondary outcomes

The secondary outcomes include the time until normal diet is resumed, time until normal activities are resumed and occurrence of adverse events (rash, vomiting, diarrhoea and anaphylaxis) and microbial recolonization of the tonsillar niche.

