### Follow-up

During discharge, a questionnaire will be provided to the persons legally responsible for the participating child. This will be filled out daily and will be presented to the investigator at follow-up visits. The questionnaire is translated, adopted and modified from the standardized Linden et al. [10] post-tonsillectomy follow-up questionnaire (Additional file 1).

On day 7, the wound bed and the general health status will be inspected by the study doctor at the Department of Otolaryngology at KCMC and ALMC respectively. On day 14, a third swab (Copan ESwab; Copan Italia SPA) of the surgical site will be taken and sent to the microbiology research laboratory for culture and sensitivity analysis, as already described. During both visits, detailed information will be obtained by the study doctor. The entire process from patient allocation to follow-up is displayed in Fig. 1 and well described in a SPIRIT (Standard Protocol Items: Recommendations for Interventional Trials) figure in Fig. 2.

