### Statistical analysis

Continuous variables will be presented as means and standard deviation or median and interquartile range (IQR) if not normally distributed. Categorical data will be presented as a number with percentage. All analysis will be done according to an intention-to-treat protocol.

Differences between the observed risks of events (for primary outcomes of bleeding and fever) between the placebo and antibiotics groups will be calculated along with their 95% confidence intervals. Absolute risks will also be presented as it is important to be aware of the underlying risk of events. Differences in pain score between the two treatment arms will be calculated as mean differences with 95% CIs, using Student’s *t* tests. Secondary outcomes will be analysed using chi-squared tests for categorical data (return to normal activities and microbial recolonization) or Wilcoxon rank-sum tests (days to return to normal diet) for continuous data. *P* < 0.05 will be considered statistically significant. All data will be coded to maximize confidentiality. Collected data will be entered into a database and analysed using IBM SPSS Statistics version 24.

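### Time to normal activities is defined as a time but assigned a chi-squared test with no cut-off day, so the comparison is undefined and loses information

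*Protocol article*

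**What the plan says.** Protocol article, Secondary outcomes, defines the two recovery outcomes in the same terms: "The secondary outcomes include the time until normal diet is resumed, time until normal activities are resumed". Both are times.

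Statistical analysis then separates them. Activities is placed with the categorical outcomes: "Secondary outcomes will be analysed using chi-squared tests for categorical data (return to normal activities and microbial recolonization"). Diet is placed with the continuous ones, under "Wilcoxon rank-sum tests (days to return to normal diet) for continuous data". No day or cut-off is attached to the chi-squared test. The same section states that "All analysis will be done according to an intention-to-treat protocol".

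Follow-up describes the data source, a caretaker questionnaire: "This will be filled out daily and will be presented to the investigator at follow-up visits". The last scheduled visit is two weeks after surgery: "On day 14, a third swab (Copan ESwab; Copan Italia SPA) of the surgical site will be taken".

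**The concern.** The named test does not fit the outcome as defined. A chi-squared test needs categories, and a time becomes categorical only once a day is fixed. None is fixed here, so two analysts following this text could compare the arms at day 7 or at day 14, or cross-tabulate by day and ignore the order, and reach different answers. The choice could also be made after the results are known.

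The text also gives no reason why two outcomes defined alike and covered by one daily questionnaire should be analysed differently.

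The direction matters. The study objective is to show that placebo is non-inferior to amoxicillin for morbidity. A blunt test on a supporting recovery outcome makes it easier to report no difference when children on placebo do return to normal activities later.

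**Working it through.** **1. Text against text**

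| Outcome | Defined as | Data | Test named | Cut-off day |
|---|---|---|---|---|
| Normal diet | time | daily questionnaire | rank-sum on days | not needed |
| Normal activities | time | daily questionnaire | chi-squared | needed, none given |

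The mismatch is confined to the second row. The plan states no power or precision figure for either outcome, so there is none to reproduce. The figure of 121 per arm (Study sample) was derived for haemorrhage and is used below only as the number of children.

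**2. Information lost, two assumed distributions**

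Assumptions, none from the document: median 7 days on amoxicillin; true time ratio 1.25; lognormal (log SD 0.5) or Weibull (shape 2) times; days rounded up; complete follow-up to day 14; 121 per arm; two-sided 5%; 1,500 simulated trials.

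| Power | Lognormal | Weibull |
|---|---|---|
| Chi-squared, day 7 | 80.6% | 59.7% |
| Chi-squared, day 14 | 58.9% | 76.5% |
| Rank-sum, unrecovered ranked last | 92.5% | 84.2% |
| Log-rank | 90.1% | 90.9% |

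With no true difference, all of these rejected in 3.9-5.5% of trials, so the gaps are not caused by inflated error.

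For a given power, information is proportional to (1.96 + z_power)². Loss = 1 − (1.96 + z_chi)² / (1.96 + z_best)², where best is the stronger time-based test:

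- Lognormal, day 7: 1 − 2.823²/3.400² = 1 − 7.97/11.56 = 31%
- Lognormal, day 14: 1 − 2.185²/3.400² = 1 − 4.77/11.56 = 59%
- Weibull, day 7: 1 − 2.206²/3.295² = 1 − 4.86/10.85 = 55%
- Weibull, day 14: 1 − 2.682²/3.295² = 1 − 7.20/10.85 = 34%

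As a benchmark, the large-sample efficiency of a median split relative to Wilcoxon for a normal or lognormal shift is (2/π)/(3/π) = 2/3, a loss of one third.

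**3. A proportional-hazards scenario**

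Assumptions, again not from the document: Weibull shape 2.5, median 6 days on amoxicillin, hazard ratio 0.70, 121 per arm, whole days to day 14. Simulated power (3,000 trials) is 77% for log-rank, 51% for chi-squared at day 7 and 12% at day 14.

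Check by formula, with cumulative hazard H(t) = ln 2 × (t/6)^2.5 on amoxicillin and 0.7 × H(t) on placebo:

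- Day 7: H = 1.019. Recovered 63.9% against 51.0%, difference 12.9 points, SE = √[(0.639×0.361 + 0.510×0.490)/121] = 0.063, z = 2.05, power ≈ Φ(2.05 − 1.96) = 54%. This agrees with the simulation.
- Day 14: H = 5.765. Unrecovered exp(−5.765) = 0.3% against exp(−4.035) = 1.8%, or about 0.4 and 2.1 children per arm. Almost nothing is left to compare, hence the low power.
- Log-rank: about 239 recoveries, z = |ln 0.70| × √(239/4) = 2.76, power ≈ Φ(0.80) = 79%. Ties from whole-day recording bring it to about 77%.

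By the formula in step 2, the loss here is 1 − 1.985²/2.699² = 46% at day 7 and 1 − 0.785²/2.699² = 92% at day 14. With medians of 5 or 7 days, log-rank stays near 77%, while chi-squared gives 42-60% at day 7 and 0-39% at day 14.

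**The case against.** **The diet analysis.** A reader might infer that the rank-sum test for diet is also wrong because it makes no provision for children who have not resumed a normal diet or are lost. The documents do not support that. Rank-sum uses the full order of days. With a common end at day 14, ranking unrecovered children last is valid and needs no invented times; in step 2 it gave 84-93% power against 90-91% for log-rank. Power falls (to 75% lognormal, 42% Weibull) only if those children are dropped. Nothing says they would be, and the intention-to-treat statement points the other way. A plain rank-sum test cannot use the partial follow-up of a child lost before recovery, and Study limitations expects some losses. But censoring and missing-data rules are commonly left to the full protocol or SAP, so the article's silence is not a fault.

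**The size.** A reader might also infer that most of the information is discarded. That holds in some scenarios, not in general: steps 2 and 3 range from 31% to 92%, and the highest value needs a day-14 cut-off that the text never states. Step 3 also simulates proportional hazards, which favours log-rank; with median 6 days, rank-sum with the unrecovered ranked last reaches about 67% rather than 77%. Every recovery input is assumed.

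**The importance.** Both outcomes are secondary. This is correct and limits the point.

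**What remains.** None of this removes the mismatch for activities. The article named a test for this outcome, and that test does not fit the outcome's own definition. That is a statement to correct, not a detail left out.

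**Conclusion.** The point stands for time to normal activities only. The outcome is defined as a time, is covered by a daily questionnaire, and is assigned a categorical test with no cut-off day. The comparison is therefore undefined, open to a choice of day after the data are seen, and less sensitive than either time-based test in every scenario examined. The loss is about 30-60% of the information under the two distributions in step 2, and smaller or larger under others; it depends on the unstated day, the recovery distribution and the true effect, none of which the document gives. The analyses of haemorrhage, fever and pain, and the sample size, are not affected.

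**What to change.** In Statistical analysis, take return to normal activities out of the chi-squared list and analyse it as the time already defined under Secondary outcomes. Either of these would do:

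- Kaplan-Meier curves and a log-rank test, censored at the last completed diary day; or
- the rank-sum test already named for diet, with children unrecovered at day 14 ranked last.

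Keep chi-squared for microbial recolonization. If a yes/no outcome is really intended, redefine it under Secondary outcomes as resumed by a stated day, fixed before unblinding; this settles the definition but accepts the loss of information. Using one method for both activities and diet would be sensible for consistency, though diet does not require correction.

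The cost is a change of wording before the data are unblinded. The daily questionnaire should already supply the days, and the planned software runs any of these methods.

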### Microbial isolates

During surgery, just before dissection of the tonsils, a swab (Copan ESwab; Copan Italia SPA, Brescia, Italy) will be taken from the tonsillar surface for culture and sensitivity. After the operation is completed, one dissected tonsil will be submerged in iodopovidone for around 30 s. Subsequently, the tonsil will be rinsed using sterilized normal saline and divided into two parts with a new sterile blade. Another swab (Copan ESwab; Copan Italia SPA) will be taken from the core of the tonsil.

For patients operated at KCMC, both swabs will be maintained at a temperature between 2 and 8 °C and dispatched within 30 min to the microbiology research laboratory. Samples from ALMC will be stored at a temperature between 2 and 8 °C and transported on the same day to the microbiology research laboratory. At the microbiology research laboratory, all swabs will be incubated at 37 °C for 24 h. After incubation is completed, subcultures from growing microorganisms will be prepared on agar plates. The isolated bacteria will then be Gram stained and microscopically investigated. Only pathogenic organisms will be worked up, no work-ups for normal flora will be done. Microbiological work-up will entirely adhere to the Clinical and Laboratory Standards Institute (CLSI) Performance Standards for Antimicrobial Susceptibility Testing. Antibiotic sensitivity testing will be done for all pathogenic, cultured microorganisms using the disc diffusion test [9]. Discs of the most common antibiotics will be used.

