### Postoperative management

After surgery, all patients will be kept in the ward for at least one night. Based on their clinical condition, patients will be discharged. On the ward, patients will receive their labelled medication with either 50 mg/kg amoxicillin or placebo. Medication will be taken 8-hourly for 5 consecutive days. Parents and caretakers are given instructions about the importance of continuing the medication after discharge from the hospital.

All patients will be given paracetamol three times a day and ibuprofen twice a day based on their weight for 10 days. Any additional analgesics or other treatment will be started whenever necessary at the discretion of the treating physician.

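### Microbial recolonization is tested by an unadjusted chi-squared test; stratifying on the surface swab taken before dissection costs almost nothing and may gain precision

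*Protocol article*

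**What the plan says.** The protocol article lists microbial recolonization among the secondary outcomes. Its Statistical analysis section assigns it to "chi-squared tests for categorical data (return to normal activities and microbial recolonization", with P "< 0.05 will be considered statistically significant". No covariate or stratified analysis is named for it.

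Three swabs are planned per child:

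- Surface (Microbial isolates): "just before dissection of the tonsils, a swab (Copan ESwab; Copan Italia SPA, Brescia, Italy) will be taken from the tonsillar surface".
- Core: after the operation, a swab "will be taken from the core of the tonsil".
- Outcome (Follow-up): "On day 14, a third swab (Copan ESwab; Copan Italia SPA) of the surgical site will be taken".

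Treatment starts after surgery (Postoperative management): "On the ward, patients will receive their labelled medication with either 50 mg/kg amoxicillin or placebo". The Randomization section stratifies on gender, age group, residence and centre. Baseline culture is not among these factors.

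**The concern.** The surface swab is taken after randomization but before the first study dose, under blinding, so allocation cannot have affected it. It can therefore serve as a baseline for the day-14 culture.

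The design does not balance the arms on it, and the planned test does not use it. If children who carry a pathogen at surgery are more likely to carry one on day 14, two things follow. The comparison is less precise than the collected data allow, and any chance difference in carriage between the arms stays in the estimated effect.

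What is at stake is the precision of a secondary outcome. It is, however, the outcome closest to the article's rationale about antibiotic use and resistance.

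**Working it through.** **1. The plan's own figure.** The only computed figure is the sample size for haemorrhage: rate 2.5% in both arms, margin 5%, power 0.80, alpha 0.05.

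n per arm = (z_alpha + z_power)² × 2p(1 − p) / margin²

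- One-sided alpha 0.05: (1.645 + 0.842)² × 2 × 0.025 × 0.975 / 0.05² = 120.6, so 121 per arm and 242 in total. This matches the article.
- One-sided alpha 0.025 gives 154 per arm and 308 in total, which does not match.

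The figure has no bearing on recolonization, for which no power is claimed. It supplies the 121 per arm used below.

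**2. Inputs the documents do not give (assumed).** Phi, the correlation between baseline and day-14 culture (each pathogen yes/no): 0 to 0.5. Pathogen prevalence at both times: 30%. Effect for the power column: 30% versus 15%.

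**3. Formulas.**

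- Variance ratio, adjusted to unadjusted: 1 − phi².
- Equivalent total N: 242 / (1 − phi²).
- 95% CI half-width: 1.96 × √(2 × 0.3 × 0.7 × (1 − phi²) / 121).
- Power: two-proportion normal approximation, two-sided 0.05, with 121 / (1 − phi²) per arm.
- Chance imbalance in baseline carriage: SD = √(2 × 0.3 × 0.7 / 121) = 5.89 points, so a 95% range of ±11.55 points.
- Shift in the unadjusted difference at that limit: 11.55 × phi (with equal prevalence at both times, the slope equals phi).

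| phi | Variance ratio | Equivalent N | Half-width (points) | Power | Shift at limit (points) |
|---|---|---|---|---|---|
| 0 | 1.00 | 242 | 11.55 | 80.2% | 0 |
| 0.1 | 0.99 | 244 | 11.49 | 80.6% | 1.15 |
| 0.3 | 0.91 | 266 | 11.02 | 83.8% | 3.46 |
| 0.5 | 0.75 | 323 | 10.00 | 90.1% | 5.77 |

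The phi = 0 row also gives the unadjusted analysis at every phi.

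**4. Simulation check.** 40,000 null trials per value of phi, 121 per arm, 30% prevalence, Mantel-Haenszel risk difference stratified on baseline culture.

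| phi | Type I error, unadjusted | Mean unadjusted difference | Variance ratio |
|---|---|---|---|
| 0 | 0.050 | −0.0003 | 1.00 |
| 0.1 | 0.051 | 0.0000 | 0.99 |
| 0.3 | 0.050 | 0.0001 | 0.92 |
| 0.5 | 0.050 | 0.0005 | 0.75 |

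The variance ratios agree with 1 − phi². The unadjusted test holds its level and shows no average bias.

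**5. The same point on the odds-ratio scale.** A second simulation (6,000 trials per scenario) assumed 121 per arm, baseline carriage 50%, day-14 carriage 40% on placebo and a within-stratum treatment odds ratio of 0.5. With baseline carriage raising the day-14 odds 2-, 4- or 8-fold, power was 68.1%, 63.2% and 53.6% by chi-squared. Stratified by baseline, it was 69.0%, 67.2% and 62.4%. Gains: 0.9, 4.0 and 8.8 percentage points.

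**The case against.** The strongest reply is that nothing here is wrong. A chi-squared test between randomized arms is valid, and its error rate already allows for chance imbalance. That stands. The shifts in the table are what an unlucky trial at the edge of the 95% range would show; they are not bias.

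Two further objections also stand in part.

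- **The gain is conditional.** The baseline swab samples a surface that is then removed, the day-14 swab samples the healing bed, and only pathogenic organisms are worked up. A weak association is plausible, and with it the gain is close to nil. A reader might infer that the plan certainly wastes precision; the documents give no correlation or prevalence that would support this.
- **Scoring is not defined.** A reader might infer that the test compares day-14 positivity alone and ignores what was there before. The article does not say so. Recolonization might be scored against the child's own earlier swabs, in which case baseline already enters through the outcome.

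It can also be said that adjustment of a secondary outcome belongs in a fuller protocol or analysis plan, which is not shown. That would answer a complaint about silence. Here the article names a specific test, and it is that stated choice that can be improved.

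**Conclusion.** The point holds as a conditional improvement to a secondary analysis, not as an error. The plan fixes an unadjusted test although a pre-treatment measure of the same kind is collected and not balanced by design.

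For phi from 0 to 0.5, adjustment removes between nothing and 25% of the variance. At the upper end, 242 children carry the information of about 323. At phi = 0 the simulated variance ratio is 1.00, so adjustment loses essentially nothing if the association turns out to be absent. These sizes rest on the assumed correlations, the 30% prevalence and 121 evaluable children per arm.

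A reader might go further and conclude that the planned result would be biased or its P value unreliable. The simulation contradicts that. The primary outcomes are untouched.

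**What to change.** In the Statistical analysis section:

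1. Score recolonization as pathogen present or absent on the day-14 swab.
2. Make the main comparison a Mantel-Haenszel common risk difference with 95% CI, stratified by the intra-operative surface-swab result (pathogen yes/no). The estimate is Σ w_k d_k / Σ w_k, where d_k is the risk difference between arms in stratum k and w_k = n_1k × n_0k / (n_1k + n_0k), with n_1k and n_0k the numbers in each arm.
3. Treat a missing or unusable baseline swab as its own stratum, so that every randomized child with a day-14 swab stays in.
4. Report the raw percentages and the chi-squared test as supportive results.

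Fix this before unblinding, since a covariate chosen afterwards is open to criticism. The cost is one extra line of analysis and the missing-baseline category. No new swab, visit or data item is needed, and the estimate has a closed form that can be computed from the stratum tables.

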### Study objective

The study objective is to compare the postoperative morbidity following elective (adeno)tonsillectomy in children treated with postoperative amoxicillin or a placebo in northern Tanzania. We hypothesize that placebo is non-inferior to amoxicillin in preventing postoperative morbidities following (adeno)tonsillectomy in children in northern Tanzania.

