### Primary outcomes

The primary outcome is post-(adeno)tonsillectomy morbidity, but morbidity cannot be measured as a single parameter. Postoperative haemorrhage and infection are the most important postoperative complications contributing to post-(adeno)tonsillectomy morbidity. Post-(adeno)tonsillectomy infection is difficult to define since the tonsillar beds are left to heal by secondary intention after surgery in a bacterial, mucosal environment. Typical symptoms of surgical site infection are therefore absent. Clinically worsening pain and raised temperature are thus considered features of infection. For this reason, postoperative haemorrhage, raised temperature (fever) and pain are the primary outcomes in this research.

Postoperative haemorrhage is defined using two parameters: major if warranting re-admission, blood transfusion or return to theatre for haemostasis; and minor if any recorded postoperative blood loss (i.e. spitting of blood saliva 24 h post operation). Fever is defined as temperature greater than 38 °C on 2 consecutive postoperative days or greater than 39 °C on any postoperative day, and postoperative pain is rated using the Wong-Baker FACES® Pain Rating Score.

Temperature will be taken daily by the research nurse while admitted and thereafter by the parent/caretaker with an axillary thermometer until the 7th postoperative day.

The Wong-Baker FACES® Pain Rating Scale will be used to assess children’s pain perception postoperatively. Written permission has been granted from Wong-Baker FACES Foundation for using both the English (while in hospital) and Swahili (while at home) Wong-Baker FACES® Pain Rating Scale in this study. The consequent need for analgesics will be documented by the prescribing physician.

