### Study sample

Postoperative bleeding, fever and pain were used as primary outcomes. We calculated power for all primary outcomes and only took the outcome with the largest number of participants. Based on the latest Cochrane Review, titled “Antibiotics to reduce post-tonsillectomy morbidity” [5], 2.5% of all patients who undergo an elective tonsillectomy have a significant postoperative haemorrhage. With this haemorrhage rate, a significance level (α) of 0.05, a power (π) of 0.80 and a non-inferiority margin of 5%, we calculated the number of patients in our intervention group. The group treated with antibiotics should include 121 patients, giving a total of 242 patients necessary for analysis. To allow for some loss to follow-up, the aim is to include 270 children.

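### Non-inferiority is hypothesised for postoperative morbidities (haemorrhage, fever, pain), but only haemorrhage has a margin and no rule sets a confidence limit against it

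*Protocol article*

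**What the plan says.** All references are to the protocol article.

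- *Study objective*: "We hypothesize that placebo is non-inferior to amoxicillin in preventing postoperative morbidities following (adeno)tonsillectomy in children in northern Tanzania".
- *Primary outcomes*: "postoperative haemorrhage, raised temperature (fever) and pain are the primary outcomes in this research".
- *Study sample*: "We calculated power for all primary outcomes and only took the outcome with the largest number of participants". The calculation shown is for haemorrhage. It starts from the statement that "2.5% of all patients who undergo an elective tonsillectomy have a significant postoperative haemorrhage" and uses "a significance level (α) of 0.05", power 0.80 and "a non-inferiority margin of 5%, we calculated the number of patients in our intervention group". The result is 121 per arm, 242 in total, with 270 to be enrolled. No event rate, standard deviation or margin is shown for fever or pain.
- *Statistical analysis*: bleeding and fever are to be reported as risk differences with 95% confidence intervals. Pain is to be reported as a mean difference with a 95% confidence interval, using Student's t test. After the secondary outcomes, the section gives its one criterion: P < "0.05 will be considered statistically significant". It does not mention non-inferiority or a margin.

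**The concern.** A non-inferiority hypothesis is defined by its margin, and it is decided by whether the unfavourable confidence limit stays within that margin. The plan gives a margin for one of three primary outcomes and gives no such decision rule for any of them. The one criterion it does give, a P-value threshold, answers whether the arms differ, not whether placebo is acceptably close to amoxicillin.

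The *Primary outcomes* section treats fever and pain as the features of postoperative infection, which is what an antibiotic would be expected to prevent. The trial is also meant to inform routine prescribing. If fever and pain enter the conclusion on morbidities with no margin fixed in advance, that part of the conclusion has no defined standard of proof, and a margin chosen after the results are known would not be credible.

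**Working it through.** **Inputs from *Study sample*:** haemorrhage rate 2.5%, taken as equal in both arms; margin 5%, read as 5 percentage points; α = 0.05, sidedness not stated; power 0.80; 121 per arm. Allocation is 1:1 (*Randomization*).

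**1. Reproducing the plan's figure.** n per arm = (z_α + z_β)² × 2p(1−p) / margin², with 2p(1−p) = 2 × 0.025 × 0.975 = 0.04875 and margin² = 0.0025, a ratio of 19.5.

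- One-sided 0.05: (1.645 + 0.842)² × 19.5 = 120.6, rounded up to **121**. This matches.
- One-sided 0.025: (1.960 + 0.842)² × 19.5 = 153.1, rounded up to **154**. This does not match.

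The size is therefore a non-inferiority size for haemorrhage at one-sided 0.05. That corresponds to a 90% two-sided interval, not the 95% interval planned in *Statistical analysis*.

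**2. Haemorrhage power under the planned 95% interval.** Standard error at 121 per arm = √(0.04875/121) = 0.0201, and 0.05/0.0201 = 2.491.

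- One-sided 0.05: Φ(2.491 − 1.645) = 80%.
- 95% interval: Φ(2.491 − 1.960) = **70%**.
- If all 270 were analysed (135 per arm), the 95% interval would give 75%.

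**3. What 121 per arm could support for fever and pain.** The article gives no inputs, so these are illustrations on assumed values. Supported margin at 80% power = (z_α + 0.842) × standard error.

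| Outcome | Assumption | One-sided 0.05 | 95% interval |
|---|---|---|---|
| Fever | 10% in both arms; SE = √(2 × 0.10 × 0.90/121) = 0.0386 | 9.6 points | 10.8 points |
| Pain | in SD units; SE = √(2/121) = 0.1286 | 0.32 SD | 0.36 SD |

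**4. Why the interval alone does not decide.** Suppose fever is seen in 10% of each arm (assumed). The 95% half-width is 1.96 × 0.0386 = 7.6 points, so the interval runs from about −7.6 to +7.6. The difference is zero and far from significant. Placebo would be non-inferior against a 10-point margin and not against a 5-point margin. The plan does not say which margin, or what other, applies.

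**5. Power for a claim on all three outcomes.** If each outcome must meet its margin, joint power cannot exceed that of any one of them. It is therefore at most the haemorrhage power: 80% at one-sided 0.05, or about 70% with the 95% interval.

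**The case against.** The best defence is that the planned outputs suit non-inferiority. All three primary outcomes get a 95% interval, no significance test is named for bleeding or fever, and chi-squared tests are assigned only to secondary outcomes. A t-based interval for pain is also a normal basis for a non-inferiority comparison. The P-value sentence comes straight after the secondary outcomes, so applying it to the primaries is an inference. For haemorrhage, margin and interval are both present and only the linking sentence is absent. The article is also condensed: it says power was calculated for every primary outcome, so fever and pain margins may exist in the full protocol.

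Much of this stands, and it rules out several stronger readings that a reader might infer:

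- *The primary analysis is simply a test of difference.* Only pain has a named test, and it comes with an interval.
- *The authors will read P > 0.05 as non-inferiority.* The article nowhere says so.
- *The error rate is inflated because any one outcome would suffice.* No such rule is proposed.
- *Joint power is 51%.* That is 0.8³, which assumes independence and exactly 80% for each outcome. The article says the largest sample size was taken, so the other outcomes would have at least 80%, and it treats fever and pain as features of the same infection. The figure is closer to a floor than an estimate.
- *The largest-sample statement is false, because fever would need far more patients at 5 points.* The article does not apply the haemorrhage margin to fever.

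The defence does not supply a standard for fever and pain. The article itself states the hypothesis, the three outcomes, one margin and one criterion, and that criterion does not answer the hypothesis. This is a mismatch among things stated, not merely a detail left for later. A margin belongs with the hypothesis, which is how the article treats it for haemorrhage.

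**Conclusion.** The point holds in this form. The hypothesis covers three primary outcomes; only haemorrhage has a margin, and the analysis text never sets a confidence limit against one. As written, haemorrhage can be judged against 5 points, while fever and pain cannot yield a non-inferiority conclusion.

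For haemorrhage the size of the problem follows from the article's own inputs: 121 per arm gives 80% power at one-sided 0.05 but about 70% with the planned 95% interval, which would need 154 per arm. This rests on a 2.5% rate in both arms, an absolute 5-point margin and the normal approximation that reproduces 121. The fever and pain margins in the working depend on an assumed 10% fever rate and on SD units. They show scale only and are not recommended margins.

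**What to change.** In *Statistical analysis*, replace the P-value criterion for the primary outcomes with this rule: placebo is non-inferior if the upper limit of the confidence interval for placebo minus amoxicillin lies below the stated margin.

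- **Confidence level.** Either use a 90% interval, which matches the one-sided 0.05 sizing, or keep 95% and restate haemorrhage power as about 70% at 121 per arm.
- **Margins.** Before unblinding, state the fever and pain margins used in the power calculations that *Study sample* says were done. If none were set, confine the non-inferiority conclusion to haemorrhage and report fever and pain as estimates with intervals.
- **Claim on morbidities.** This is a design choice. If the claim is kept, require each outcome to meet its own margin; no split of alpha is then needed. Say that 0.80 is the power for haemorrhage alone and that joint power is no higher.

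The cost is a few sentences in two sections, with no new patients or data. The price is a narrower conclusion or a less favourable stated power.
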